### Sensitivity analyses

A missing data analysis will investigate any patterns of missingness. For each primary and secondary outcome component with missing data, multiple imputation using multivariate regression with factors of age, gender, time, and intervention status will produce 100 estimates. Sensitivity analyses will be performed using this multiple imputation to account for missing data and then re-running the analyses.

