### Main analysis plan

Descriptive statistics will be used to summarize the characteristics of the patient-level variables and the GP clinics (clusters), see Table 2. Cluster-level variables are those used in the stratified randomization, which are four types of organizational variations, plus the intervention status of the cluster and the time since (or before) the intervention. The intraclass correlation coefficient (ICC) will be calculated and reported.

**Table 2 Tab2:** Individual and cluster-level variables available for multivariable analysis

Variable	Description
*Individual level*	
Demographics	
Sex	Sex of patient.
Age	Age of patient at survey completion date.
Country of birth	Country of birth of patient.
Ethnicity	Ethnic or cultural group that the patient identifies with.
Main language	Main language spoken at home.
Marital Status	Marital status of patient.
Living situation	Current living situation of patient.
Education	Education level of the patient.
Health Economics	
Mental health medications	Medications for mental health taken regularly by the patient.
Employment	Current working status of the patient.
Income	Usual weekly income of patient, after tax, from all sources of employment.
Days out of role	Number of days in the past month that the patient was totally or partly unable to carry out normal activities because of mental health problems.
Days absent from work	Number of days in the past month that the patient was absent from work due to illness or disability, and due to mental health problems.
Hospitalizations	Number of hospital admissions for physical problems and for mental health problems, including number of nights in total and reasons for most recent admissions.
Consultations with health professionals	Number and length of consultations with health professionals for physical health and mental health problems.
GUPI	The General-Practice Users’ Perceived-need Inventory is a one-page instrument developed to assess participants’ estimation of their needs for mental health care and the meeting of those needs.
*Cluster level*	
Cluster group	Allocated to receive the intervention at either Step 1 or Step 2.
Intervention status (0/1)	A lag time of six months is anticipated until intervention effects are possible. The intervention status variable indicates that this lag time has passed.
Dosage (%)	Intervention dosage.

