Time since intervention	All patient surveys are time-stamped in relation to the time the intervention was received at the cluster. Time value of “0” is given for the plus/minus three months from date of training; “1” for four-to-six months post training; “2” for seven-to-nine months post training, etc. Time value of “-1” for four-to-six months before training; “-2” for seven-to-nine months before training, etc.
Time	Study month that survey was completed: “0” = December 2014, “1” = January 2015, etc.
*Cluster level stratification variables*	
Clinic type	Privately owned general practice vs community health center.
GP clinic size	GP equivalent full time (EFT) size greater than 5 (yes/no).
Clinic location	Local government area location: Dandenong, Casey, Cardinia, other.
Specialist focus clinic	A specialist focus clinic (yes/no) was determined by more than 10% of the practice patients belonging to any of the following groups: a. people with HIV/AIDS b. people with enduring and serious mental illness (e.g., schizophrenia, bipolar disorder) c. people with permanent physical disabilities d. people with addictions e. homeless people f. transient/seasonal populations g. people living in poverty h. Aboriginal peoples i. recent immigrants (six months or less) j. people from cultural minorities k. people with sports injuries l. other

The primary analysis will examine the patient-level QPR scores (continuous data) at baseline, nine months (Step 1), and 18 months (Step 2), using a linear mixed-effects model. The model will include intervention status and time as fixed effects and clusters and patients as random effects. Both univariate and multivariable models will be developed based on baseline patient and cluster-level variables considered statistically significant (*p <* 0.10) or clinically important (e.g., age, sex), see Table 2, and included in the model as fixed. This will include the intervention dosage variable described earlier. Model fit will be examined by comparing AIC values.

Secondary analyses will examine the patient-level data of the INSPIRE, WEMWBS, and K10. Similar to the primary analysis, we will use linear mixed-effects models to compare the intervention and control periods (pre-intervention) for continuous outcomes and generalized linear mixed-effects models for binary outcomes.

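### The stated multiple imputation covers outcomes only, so it cannot recover patients with a missing Table 2 covariate in the multivariable models

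*Protocol article*

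**What the plan says.** All references are to the protocol article.

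**Sensitivity analyses.** The section opens with a general statement: "A missing data analysis will investigate any patterns of missingness". It then fixes the method: "For each primary and secondary outcome component with missing data, multiple imputation using multivariate regression with factors of age, gender, time, and intervention status", with 100 imputations. Its purpose is stated next: "Sensitivity analyses will be performed using this multiple imputation to account for missing data and then re-running the analyses".

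**Main analysis plan.** The basic primary model for the QPR is a linear mixed model: "The model will include intervention status and time as fixed effects and clusters and patients as random effects". Univariate and multivariable versions follow, using baseline patient and cluster "variables considered statistically significant (*p <* 0.10) or clinically important (e.g., age, sex), see Table 2, and included in the model as fixed". On model comparison the text says only: "Model fit will be examined by comparing AIC values".

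**Table 2.** Its title is "Individual and cluster-level variables available for multivariable analysis". The individual-level part has 16 entries: 8 demographic, 7 health-economic, and the perceived-need inventory (GUPI). Income, for example, is defined as "Usual weekly income of patient, after tax, from all sources of employment".

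The article does not say how a blank covariate is treated in any model, or whether the models compared by AIC share one set of patients.

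**The concern.** The article does not leave missing data to a later document. It names what is imputed, from which four factors, and how many times, and then sends the completed data back through the planned analyses. Those include models with Table 2 covariates, and the covariates are outside the imputation.

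A likelihood-fitted mixed model cannot use a record with a blank covariate unless that value is imputed or coded. A patient who gave no income is therefore as unusable in a re-run model containing income as before, however well the QPR has been imputed. Blanks are plausible. The survey takes about 45 minutes, and a patient without a job may leave income from employment and days absent from work empty.

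At stake are the precision of the adjusted effect and the population it describes. A sensitivity analysis meant to account for missing data would deal with only one of the two places where data can be missing.

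**Working it through.** **1. Inputs from the document**
- SD 16, ICC 0.05, two steps, three cross-sectional waves, two-sided 0.05, power 0.80 (Sample size targets).
- Original minimum: 20 clusters x 1 GP x (10 + 10 + 10) = 600 patients, which reproduces the stated 600.
- Current target: 30 GPs (Adaptations to GP recruitment and retention) x 30 patients each (Adaptations to sample size targets) = 900. The article does not state this total. Over 18 clusters x 3 waves it is 900/54 = 16.7 patients per cluster and wave.
- Covariate missingness: not given. Every rate below is an assumption.

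**2. Standard error if patients are lost**

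The stepped-wedge (Hussey-Hughes) variance, with I clusters, T = 3 waves, s² = 16² x 0.95/n and t² = 16² x 0.05 = 12.8, is

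Var = I s²(s² + T t²) / [(IU - W)s² + (U² + ITU - TW - IV)t²].

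For 18 clusters, 9 per sequence (0,1,1 and 0,0,1):
- U = 27, W = 9² + 18² = 405, V = 9 x 4 + 9 x 1 = 45.
- IU - W = 486 - 405 = 81.
- U² + ITU - TW - IV = 729 + 1458 - 1215 - 810 = 162.

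| Patients lost (assumed) | n per cluster and wave | s² | SE | Increase |
|---|---|---|---|---|
| 0% | 16.7 | 14.59 | 2.07 | - |
| 10% | 15.0 | 16.21 | 2.17 | 4.9% |
| 15% | 14.2 | 17.17 | 2.23 | 7.7% |
| 20% | 13.3 | 18.24 | 2.29 | 10.7% |

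First row in full: 18 x 14.59 x (14.59 + 38.4) / (81 x 14.59 + 162 x 12.8) = 4.28, and the square root is 2.07.

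**3. How losses build up over several covariates**

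If each of k covariates is missing independently at rate m, the complete share is (1 - m)^k. From 600 patients:
- 5 covariates at 2%: 600 x 0.98^5 = 542.
- 5 covariates at 5%: 600 x 0.95^5 = 464.
- 8 covariates at 5%: 600 x 0.95^8 = 398.

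For 20 clusters with 10 patients per wave, the same variance formula gives a detectable difference of 6.93 QPR points (0.43 SD) at power 0.80. At that difference, power in the three cases is 0.76, 0.70 and 0.64. These are illustrations. Real blanks tend to fall on the same patients, which would make the loss smaller than independence implies.

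**4. AIC, the secondary matter**

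At SD 16 each patient contributes about ln(2 x pi x 256) + 1 = 7.38 + 1 = 8.38 to minus twice the log-likelihood, against a penalty of 2 per parameter. Dropping 1% of 600 (6 patients) lowers AIC by about 50, and 5% (30 patients) by about 251, whatever the fit.

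A simulation of 200 runs (600 patients, 20 clusters) agrees. A pure-noise covariate with 1% missing beat the model without it in 100% of runs when the patient sets differed. With both models fitted to the same patients, it won in 15-19% of runs across missing rates of 1-10%.

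**The case against.** The strongest reply is that much of the damage would come from a software default, not from the plan. Four parts of it stand.

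- **Imputation is only a sensitivity analysis.** A reader might infer that, because covariates are not imputed, the primary model drops every patient with a blank covariate. That does not follow. The scope of a sensitivity analysis does not determine how the primary model treats covariates, and the article nowhere states listwise deletion.
- **AIC on differing patients is not planned.** A reader might infer that the comparison will reward the covariates with most blanks. The text is silent, and one common set of patients is compatible with it. Covariates enter by p below 0.10 or clinical importance; AIC is named only for examining fit. Taken alone, this is a detail that an article may leave to the analysis plan.
- **Exposure is limited.** Table 2 lists candidates, and only those selected enter a model. The basic model needs only intervention status and time, so it loses no one for this reason. Patients are asked for best estimates (Measures), and medication details can come from GP records with consent (Data collection and management). Both reduce blanks.
- **No rate is given.** The size of the loss is therefore assumed, and no bias in the treatment effect has been shown.

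What does not stand is the claim that the whole matter is mere silence. The article specifies the imputation and limits it to outcomes. Followed as written, the re-run multivariable models still cannot use a patient with a blank covariate. The planned look at missingness patterns describes that problem but does not remedy it.

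**Conclusion.** The point holds in a limited form. The stated imputation leaves missing Table 2 covariates unaddressed, so it cannot recover those patients when the multivariable models are re-run. Unless the values are handled in some other way, the adjusted effect rests on patients complete for every covariate in the model.

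The cost in precision is moderate: about 5-11% on the SE for an assumed loss of 10-20%, under the design SD and ICC and a target of 900 patients spread evenly over 18 clusters. It could be larger if several incomplete covariates enter together. The estimate without patient covariates is untouched.

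The AIC matter is a clarification, not an error in the plan. The distortion would be large if patient sets differed, but nothing in the article says that they will.

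**What to change.** In Sensitivity analyses, extend the imputation to the covariates used in the multivariable models and impute them jointly with the outcomes. A separate missing category is not a good substitute. Each wave is a new sample recruited through unblinded GPs, so the compared groups may differ, and such a category can leave residual confounding.

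As a secondary clarification, add one sentence to Main analysis plan saying that AIC is compared only between models fitted to the same patients.

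The cost is a few more variables in the imputation step and one sentence of text. No new data are needed.

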## Methods

### Overall design

The intervention mixed methods design involves a stepped-wedge cluster randomized controlled trial testing the outcomes of training in recovery-oriented practice, together with an embedded qualitative study to identify the contextual enablers and challenges to implementing recovery-oriented practice within primary care settings. Eighteen general practices and community health centers were randomly allocated to one of two steps (9 months apart) to start an intervention comprising general practitioner training in the delivery of recovery-oriented practice. Data collection consists of cross-sectional surveys collected from patients of participating general practitioners at three time points: baseline, and again at the end of Steps 1 and 2 (see Fig. 1). A mixed methods design was chosen for a number of reasons, including that it would produce richer and more complete findings than that based on either the qualitative or quantitative approach alone. Combining these approaches can further explain and enhance the integrity of the project outcomes, so that a mixed methods design may assist with project credibility, particularly when multiple stakeholders are involved such as in the PULSAR project [28]. The use of qualitative and quantitative methods were integrated at different stages of the intervention trial [27]. Initially, qualitative methods were used in an exploratory manner to identify potential barriers to recovery-oriented training within primary care settings, and to inform the intervention design. Subsequently, quantitative methods are being used to then measure the effectiveness of the intervention. Following the intervention trial, qualitative methods will be used in an explanatory manner to gain a more nuanced understanding of GP experiences of implementing recovery-oriented practices and patient experiences of these practices [28]. Quantitative and qualitative data are collected from patient participants, but only qualitative data are collected from GP participants.

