#### Sample size targets

The study has two sample groups: GPs and patients of these GPs. Sample size calculations were done using Stata statistical software *stepped-wedge*: for clusters defined at the level of the general practice site, the primary outcome measure is the QPR, with a published mean of 46 and standard deviation of 16, power of 0.80, significance level set at 0.05, intraclass correlation coefficient (ICC) within practice sites of 0.05, the number of steps (2), and patient data collected cross-sectionally at three time points (baseline, Step 1, and Step 2).

The original sample target was a minimum of 20 different sites (clusters) with one GP per site; each GP was required to recruit a minimum of 30 patients during the four-year project (10 patients at baseline, 10 at Step 1, and 10 at Step 2), resulting in a minimum of 600 patient participants overall.

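### The listed imputation factors omit the cluster, so the missing-data sensitivity analysis dilutes the ICC and can bias the effect if scores are missing more often in some practices

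*Protocol article*

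**What the plan says.** Under Sensitivity analyses, the protocol article states that, for each primary or secondary outcome component with missing data, "multiple imputation using multivariate regression with factors of age, gender, time, and intervention status will produce 100 estimates". It continues: "Sensitivity analyses will be performed using this multiple imputation to account for missing data and then re-running the analyses".

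The analyses to be re-run are those of the Main analysis plan, where "The model will include intervention status and time as fixed effects and clusters and patients as random effects". That section also says the ICC will be calculated and reported. The sample size was planned with an "intraclass correlation coefficient (ICC) within practice sites of 0.05" (Sample size targets).

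No section adds the practice, or the variables that stratified the randomization, to the imputation factors.

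**The concern.** The analysis model treats patients of one practice as correlated, while the stated imputation model treats them as independent once the four factors are known. Time and intervention status say which period and condition a survey belongs to, but not which practice. Two consequences follow.

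- **Diluted clustering.** An imputed score carries no practice effect, so imputed data look less clustered than the real data, and standard errors and the ICC are estimated from those data.
- **A possible shift in the effect.** A missing score in a low-scoring practice is drawn around the average of all practices in that period and condition. If such practices have more missing scores after training than before, their post-training means are pulled up and the intervention effect is inflated.

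Part of any gap between the imputed and the primary result would then come from the imputation model, although readers would take it as evidence about missing data.

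**Working it through.** **Inputs from the protocol article.** "Eighteen general practices and community health centers were randomly allocated to one of two steps (9 months apart"); 30 GPs recruited (Adaptations to GP recruitment and retention); "10 patients at baseline, 10 at Step 1, and 10 at Step 2" per GP; ICC 0.05; QPR with a "published mean of 46 and standard deviation of 16"; "power of 0.80, significance level set at 0.05". With 30 GPs, a cluster has on average 30 x 10 / 18 = 16.7 surveys per period.

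**Assumed, because the article does not say.** The missing share and its pattern; a two-sided test; an equal split of clusters between the steps.

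**Step 1: a yardstick.** The article describes its detectable effect only in words, so there is no numerical effect size to reproduce. (Its original target does reproduce: 20 sites x 30 patients = 600.) The Hussey-Hughes variance for I clusters and T periods is

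Var = I s²(s² + Tτ²) / [(IU - W)s² + (U² + ITU - TW - IV)τ²]

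where U is the number of treated cluster-periods, W the sum of squared treated counts by period, and V the sum of squared treated counts by cluster.

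- I = 18, T = 3, U = 27, W = 405, V = 45.
- τ² = 0.05 x 256 = 12.8; s² = 0.95 x 256 / 16.7 = 14.6.
- SE = 2.07 points; detectable difference = (1.96 + 0.84) x 2.07 = 5.8 points (0.36 SD).

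**Step 2: ICC shrinkage.** After imputation without cluster, two patients of one practice share its effect only if both scores were observed. If missingness is independent across patients with share p, the within-practice covariance becomes (1 - p)² times its true value, while the total variance is about unchanged. So ICC after imputation ≈ ICC x (1 - p)².

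| True ICC | p | Formula | Simulated |
|---|---|---|---|
| 0.05 | 5% | 0.045 | 0.045 |
| 0.05 | 10% | 0.041 | 0.040 |
| 0.05 | 30% | 0.025 | 0.025 |
| 0.15 | 10% | 0.122 | 0.122 |
| 0.15 | 30% | 0.074 | 0.074 |

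**Step 3: effect estimate.** Three separately built simulations used a random-intercept model, 18 clusters and three periods. None included age or gender as predictors of missing scores, as far as their settings are stated.

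- A: 30 GPs x 10 surveys per period, true effect 0.40 SD, 500 replications, 15 imputations.
- B: 16 patients per cluster-period, true effect 5 points, 400 replications, 20 imputations.
- C: 16 patients per cluster-period, true effect 0.40 SD, 300 replications, 15 imputations.

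The Monte Carlo error of the bias is about 0.13 points in B and C. Results at ICC 0.05, imputing without cluster:

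| Missingness | Run | Bias (QPR points) | Coverage |
|---|---|---|---|
| 5% at random | C | 0.00 | not recorded |
| 10% at random | C | -0.03 | 95.3% |
| 10% at random | B | +0.08 | 92.2% (full data 93.8%) |
| 30% at random | B | -0.02 | 94.3% |
| 30%, varying by practice | B | -0.16 (complete cases -0.16) | 91.2% (complete cases 92.7%) |
| After training 15% in low-scoring practices, 5% in others; 8% before | C | +0.11 | 95.0% |
| 30%, depending on practice level after training | B | +0.68 | 93.2% |
| After training 45% in low-scoring practices, 10% in others; 15% before | C | +0.51 | 95.7% |
| Same 45/10/15 pattern | A | 0.05 SD x 16 = +0.8 | 93% |

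The Monte Carlo error of a coverage figure is about 1 percentage point, e.g. √(0.95 x 0.05 / 400) = 1.1 in B.

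**Step 4: with practice indicators in the imputation model.** At ICC 0.05, the +0.68 in B becomes -0.21, with coverage 94.8%. In A the estimate returns to 0.40-0.41 SD, with coverage 95%. At 30% missing at random, the SD of the shift from the complete-case estimate falls from 0.71 to 0.54 points. The re-estimated ICC is 0.06 (A) to 0.07 (B), a slight overstatement.

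**Step 5: higher ICC, as a range.** At ICC 0.15 (B), bias under practice-dependent missingness is +1.27 without cluster and -0.22 with it. At ICC 0.10 (A), coverage is 90% without cluster and 94% with it. The article assumes neither ICC.

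**The case against.** The strongest reply is that little may be missing. The surveys are cross-sectional, so there is no follow-up dropout, and a patient who declines returns nothing and is not a row to impute. What is imputed is a missing score on a returned survey. A reader might infer heavy, practice-dependent missingness from the uneven results described under Challenges with patient recruitment and retention, but that passage concerns recruitment and survey distribution. This objection stands: the high-missingness figures are a scenario, and at 5-10% missing at random no bias can be detected. At 10%, no trial in B moved by more than 1 point from its complete-case estimate.

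Second, multivariate regression may mean that the outcomes are imputed jointly, so that observed scales carry practice information. The text allows this reading without settling it. With one observed scale assumed to correlate 0.75 with the QPR, run C's 45/10/15 pattern gave a bias of +0.19 (complete cases +0.13) and an ICC of 0.041. Joint imputation would therefore reduce the problem considerably in that setting.

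Third, coverage differences at ICC 0.05 are close to simulation error, so the coverage case is weak at the design value. This also stands.

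A reader might go further and infer that the imputed analysis does not test sensitivity to missing data, since it assumes missing at random much as the mixed model does. The documents do not support stating that as an error. Wanting a different missingness assumption is a separate preference, imputation with the cluster would rest on the same one, and the article also plans an analysis of missingness patterns.

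None of this supplies the missing cluster term. The factor list is written out and conflicts with the model to be re-run.

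**Conclusion.** The point holds in limited form. The stated imputation model is incompatible with the stated analysis model. Shrinkage of the ICC by about (1 - missing share)² follows directly from the mechanism and agrees with simulation.

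Bias in the effect is conditional. It is near zero when scores are missing at random across practices. It reaches about 0.5-0.8 QPR points at ICC 0.05 only when missingness is heavy and concentrated in low-scoring practices after training. Against the 5.8-point detectable difference, that is 0.5/5.8 = 9% to 0.8/5.8 = 14%. Joint imputation of the outcomes would make it smaller.

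A reader might infer that the primary result is compromised. It is not: the primary mixed model includes the cluster, and its complete-case bias at ICC 0.05 was at most 0.16 points in run B, within about one Monte Carlo error. These sizes rest on assumed missing shares, which the article does not give.

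**What to change.** Add the cluster to the imputation model, preferably as a random practice intercept. Practice indicators are acceptable, with a note that they overstate the ICC somewhat (about 0.06-0.07 against 0.05). Keep age, gender, time, intervention status and the 100 imputations, and state that each imputed dataset is analysed with the primary mixed model and the results combined.

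Two additions are optional: the other scales as predictors, if the outcomes are not already imputed jointly, and the patient recruitment group, if it is recorded (Table 2 does not list it). Reporting the share of missing scores by practice and period would show readers which part of the range above applies.

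The cost is one sentence in the plan and a few lines of code, with no new data needed for the main change. If a separate analysis plan already includes the cluster, the published factor list should be brought into line with it.

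### The imputation model for the missing-data sensitivity analysis omits practice, so where whole scores are missing the imputed data understate the ICC and the interval is slightly too narrow

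*Protocol article*

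**What the plan says.** The Sensitivity analyses section of the protocol article first promises a look at how data are missing: "A missing data analysis will investigate any patterns of missingness". For every primary and secondary outcome component with gaps it then sets the imputation method, the factors and the number of imputations: "multiple imputation using multivariate regression with factors of age, gender, time, and intervention status will produce 100 estimates". The use of the result is also stated: "Sensitivity analyses will be performed using this multiple imputation to account for missing data and then re-running the analyses".

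The analyses to be re-run are defined under Main analysis plan: "The model will include intervention status and time as fixed effects and clusters and patients as random effects". The same section says of the ICC: "The intraclass correlation coefficient (ICC) will be calculated and reported". Under Sample size targets the design assumes an "intraclass correlation coefficient (ICC) within practice sites of 0.05".

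No expected share of missing scores is given anywhere.

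**The concern.** The imputation is single-level and the analysis is multilevel. With practice left out, a missing score is drawn around the mean for its time point and intervention status across all practices, with independent error. A patient from a high-scoring practice is imputed as if from an average one. The practice effect in the completed data is therefore diluted, the ICC estimated from those data is too low, and the imputed values add noise to the training contrast that the pooled standard error does not fully reflect.

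At stake is whether the imputed re-analysis is a fair check on the main result. A sensitivity analysis should not be less well calibrated than the analysis it checks. The ICC is also a result in its own right, and the imputed version would mislead anyone who used it to plan a later trial.

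**Working it through.** **Inputs from the article.** QPR mean 46, SD 16, power 0.80, significance level 0.05 and ICC 0.05 (Sample size targets); 18 practices and two steps (Overall design); 10 patients per GP per period (Sample size targets); 30 GPs (Adaptations to GP recruitment and retention). This gives 30 × 10 / 18 ≈ 17 patients per practice per period.

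**Assumptions.** Nine practices per step, a two-sided test, and missing shares m of 5-30%.

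**The plan's own figure.** 20 sites × 30 patients = 600, as stated. The power claim cannot be reproduced because no target difference is given. With the Hussey-Hughes variance, 20 practices × 10 per period and ICC 0.05 give a detectable difference of 6.93 points (6.93/16 = 0.43 SD).

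**Step 1: effect on the ICC when whole scores are missing.** Two patients of one practice share the practice covariance only if both scores are observed, which has probability (1-m)². The total variance is nearly unchanged. So ICC(imputed) ≈ ICC × (1-m)², a relative fall of 1-(1-m)²:

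- m = 5%: 1-0.95² = 0.0975, about 10%
- m = 10%: 1-0.90² = 0.19
- m = 20%: 1-0.80² = 0.36
- m = 30%: 1-0.70² = 0.51

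**Step 2: how far the standard error depends on the ICC.** With s² = residual variance / n, practice variance t², I practices and T periods, the variance of the effect is

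I s²(s² + T t²) / [(IU - W)s² + (U² + ITU - TW - IV)t²].

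For 18 practices and 3 periods, U = 27, W = 405 and V = 45, so the bracket is 81 s² + 162 t².

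- ICC 0.05: t² = 12.8, s² = 243.2/17 = 14.31; variance 4.20, SE 2.05.
- ICC 0.025: t² = 6.4, s² = 249.6/17 = 14.68; variance 4.02, SE 2.01.

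Halving the ICC lowers the SE by only about 2%, because much of the training effect is estimated within practices.

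**Step 3: simulation.** ICC 0.05, SD 16, scores missing completely at random. Imputation was by normal regression on time and intervention status without practice; age and gender were omitted as carrying no signal. There were 20 imputations, a random-intercept REML refit, Rubin's rules, and 3,000 replicates per row. The 10 × 30 layout reflects the reduced minimum number of clusters.

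| Practices × patients per period | m | ICC imputed / full | SE / empirical SD, imputed | Coverage, imputed | SE / empirical SD, complete case | Coverage, complete case |
|---|---|---|---|---|---|---|
| 18 × 17 | 10% | 0.81 | 1.00 | 95.5% | 1.01 | 95.7% |
| 18 × 17 | 20% | 0.64 | 0.98 | 94.9% | 1.00 | 95.1% |
| 18 × 17 | 30% | 0.49 | 0.934 | 92.8% | 0.974 | 94.0% |
| 10 × 30 | 10% | 0.81 | 0.97 | 94.1% | 0.98 | 94.3% |
| 10 × 30 | 20% | 0.64 | 0.95 | 93.3% | 0.98 | 94.2% |
| 10 × 30 | 30% | 0.49 | 0.914 | 92.4% | 0.962 | 93.6% |

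The ICC column matches Step 1. Simulation error is about 0.4 percentage points on coverage (√(0.95 × 0.05/3000)) and about 1.3% on the SE ratio (1/√(2 × 3000)).

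At 30% missing the reported SE is 7-9% too small (1-0.934 and 1-0.914), against 3-4% for complete cases (1-0.974 and 1-0.962). The pooled SE is only 1.1-1.5% below the complete-case SE (ratios 0.989 and 0.985). Most of the remainder is extra variability of the estimate: 0.985 × 0.974 / 0.934 = 1.03 and 0.989 × 0.962 / 0.914 = 1.04.

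With missingness very uneven across practice-periods (18 × 17), coverage was 94.2%, 93.5% and 92.6% at 10%, 20% and 30% missing.

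**Step 4: if items rather than whole scores are missing.** A smaller check (25-30 replicates per setting) used 22 items, an assumed inter-item correlation of 0.3-0.4, and joint normal imputation without practice. The ratio of imputed to full-data ICC was 0.999 with 1% of items missing (1-0.99²² = 20% of totals incomplete), 0.996 with 2% (36% incomplete) and 0.98-0.99 with 5% (68% incomplete). With 20% of patients missing every item it was 0.60, in line with Step 1 given so few replicates.

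**Step 5: adding practice.** With practice indicators and scores missing at random at 10-30%, the ICC was 1.05-1.31 times the full-data value, SE / empirical SD was 0.98-1.00 and coverage was 93.8-94.9%. A random-intercept imputation was not simulated.

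**The case against.** The strongest counter-argument concerns what is actually missing. Patients who return no survey never enter this cross-sectional dataset, so many gaps may be skipped items in returned surveys. The article speaks of outcome components and multivariate regression, which can be read as joint imputation of items. The patient's own answers then carry the practice effect, and the loss of ICC is under 2% (Step 4). This stands as a condition on the size. It does not remove the mismatch: the wording is ambiguous, other items are not among the named factors, and surveys with a whole scale left blank remain exposed.

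Second, the article is a condensed account and does not say that the four factors are the only ones. That is fair, and if the full analysis plan includes practice the point falls away. But the text does not leave the imputation model open. It fixes method, factors and number of imputations, and practice is absent.

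Third, this is only a sensitivity analysis, and the primary model already has a random cluster effect. That stands fully.

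Fourth, practice indicators bring an error of their own, an inflated ICC. That also stands, but it errs on the cautious side for the interval.

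**Conclusion.** The mismatch is real and the consequence is minor. Where whole scores are missing, the ICC from the imputed data is too low by about 1-(1-m)², and the interval for training is negligibly too narrow at 10% missing and about 7-9% too narrow at 30%, with coverage near 92.5%. These sizes rest on assumed missing rates, an ICC of 0.05, and age and gender carrying little information about practice.

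Several stronger readings are tempting and are not supported:

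- **The plan halves the ICC.** A fall of 20-50% requires about 10-30% of whole scores to be missing, and no rate is stated. At 5% the fall is about 10%.
- **The lost clustering makes the interval seriously too narrow.** In this design the SE moves only from 2.05 to 2.01 when the ICC is halved.
- **The imputation is the only look at missing data.** The article also plans an examination of missingness patterns.
- **The trial's main result is compromised.** No primary estimate, interval or p value depends on this imputation.

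**What to change.** In the Sensitivity analyses section, add practice (cluster) to the imputation factors, preferably as a random intercept in a multilevel imputation. If the software routine cannot do that, use practice indicator variables. Report the ICC from the imputed data beside the ICC from the observed data, so that any dilution or inflation is visible.

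The cost is one line of text and somewhat longer run time; no new data are needed and the primary analysis does not change. The downside of indicators is that they overstate the ICC somewhat (about 1.05-1.31 times the full-data value in Step 5), so intervals err slightly on the cautious side. They also cannot be estimated for a practice with no observed score. A random intercept should largely avoid both problems, though that was not simulated here.
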